# Effectiveness of the Dader Method for pharmaceutical care in patients with bipolar I disorder: EMDADER-TAB: study protocol for a randomized controlled trial

**DOI:** 10.1186/1745-6215-15-174

**Published:** 2014-05-20

**Keywords:** Bipolar disorders, Drug-related problems, Pharmaceutical care, Pharmacotherapy follow-up, Community pharmacy services, Pharmacists, Outpatients

## Abstract

**Background:**

Bipolar I disorder (BD-I) is a chronic mental illness characterized by the presence of one or more manic episodes, or both depressive and manic episodes, usually separated by asymptomatic intervals. Pharmacists can contribute to the management of BD-I, mainly with the use of effective and safe drugs, and improve the patient’s life quality through pharmaceutical care. Some studies have shown the effect of pharmaceutical care in the achievement of therapeutic goals in different illnesses; however, to our knowledge, there is a lack of randomized controlled trials designed to assess the effect of pharmacist intervention in patients with BD. The aim of this study is to assess the effectiveness of the Dader Method for pharmaceutical care in patients with BD-I.

**Methods/design:**

Randomized, controlled, prospective, single-center clinical trial with duration of 12 months will be performed to compare the effect of Dader Method of pharmaceutical care with the usual care process of patients in a psychiatric clinic. Patients diagnosed with BD-I aged between 18 and 65 years who have been discharged or referred from outpatients service of the San Juan de Dios Clinic (Antioquia, Colombia) will be included. Patients will be randomized into the intervention group who will receive pharmaceutical care provided by pharmacists working in collaboration with psychiatrists, or into the control group who will receive usual care and verbal-written counseling regarding BD. Study outcomes will be assessed at baseline and at 3, 6, 9, and 12 months after randomization. The primary outcome will be to measure the number of hospitalizations, emergency service consultations, and unscheduled outpatient visits. Effectiveness, safety, adherence, and quality of life will be assessed as secondary outcomes. Statistical analyses will be performed using two-tailed McNemar tests, Pearson chi-square tests, and Student’s t-tests; a *P* value <0.05 will be considered as statistically significant.

**Discussion:**

As far as we know, this is the first randomized controlled trial to assess the effect of the Dader Method for pharmaceutical care in patients with BD-I and it could generate valuable information and recommendations about the role of pharmacists in the improvement of therapeutic goals, solution of drug-related problems, and adherence.

**Trial registration:**

Registration number NCT01750255 on August 6, 2012. First patient randomized on 24 November 2011.

## Background

Mental illness is one of those medical conditions with difficult management and approaches due to characteristics related to the patient, such as insight of illness [1], therapeutic non-compliance, self-medication, inadequate family environment, poor social support, use and abuse of psychoactive drugs, and distrust of medical, pharmacological, and non-pharmacological therapy. Other circumstances that complicate the management of mental illnesses are the side effects and adverse reactions to drugs used in treatment. Hence, with the goal of contributing to controlling, reducing, and improving the current and future conditions of patients with any kind of mental disorder, there is a need for monitoring and following up on the outcomes obtained by psychiatrists using drug therapy [2]. In addition, these proposals should involve all phases of the health-disease process: education, mental health promotion, prevention, diagnosis, treatment, and rehabilitation of mental illness [2]. Mental disorders represent a high burden of disability, morbidity, and mortality worldwide [3].

Bipolar disorder (BD) is a known severe chronic mental illness. People with BD experience drastic alterations in mood and a decrease in labor and social performance [4]. It is manifested by the presence of both depressive and manic episodes, mixed or hypomanic episodes, usually separated by asymptomatic intervals. In BD-I there is at least one manic episode, in BD-II there are at least one hypomanic or mixed episode and a depressive episode [5]. According to the World Health Organization (WHO), BD ranks as the sixth leading cause of disability-adjusted life years (DALYs) worldwide among all diseases (for the population aged 15 to 44 years), and life expectancy is significantly reduced for those who suffer this condition. In addition, between 25% and 50% of patients attempt suicide and about 15% commit it [6]. The last article published based on a survey of 61,392 adults from 11 countries, found that the total lifetime prevalence of bipolar disorder spectrum was 2.4% worldwide, a combination of prevalence rates of 0.6% for BD-I, 0.4% for BD-II, and 1.4% for sub-threshold bipolar disorder. Twelve-month prevalences were 0.4% for BD-I, 0.3% for BD-II, 0.8% for subthreshold BD, and 1.5% for BD spectrum [7]. BD-I patients are more likely to have poor adherence included rapid cycling, suicide attempts, and current anxiety or alcohol use disorder. Additionally, a mental health study conducted in Colombia in 2003, found that the lifetime prevalence of BD-I is 1.8% (2.1 in men and 1.8 in women); and BD-II corresponds to 0.2% (0.1 in men and 0.2 in women). The bipolar spectrum (BD-I, BD-II, cyclothymia, and others not specified) varies from 3% to 6.5% [8].

The pharmacist can contribute to the management of this problem by working with the psychiatrist and the multidisciplinary team responsible for the patient’s care (psychologist, nurses, occupational therapist, social worker, and nutritionist, among others) [9,10]. The pharmacist should guide efforts to achieve and implement interventions to maximize drug therapy outcomes, such as informing the patient verbally and in writing about the proper use of medications, assessing and improving the therapeutic adherence, following the effectiveness and safety of pharmacotherapy, and giving feedback to the physicians responsible for the patient’s treatment. There are several studies that highlight the role of pharmacists in achieving therapeutic goals, and their inclusion on the health team improves the appropriate use of medication and treatment adherence. Likewise, there are some studies of patients with mental illness showing that pharmacists, through pharmaceutical care, may reduce suicide risk and minimize relapses [11-13].

Pharmaceutical care is a professional practice in which the pharmacist takes responsibility for a patient’s medication-related needs. This is achieved by detecting, preventing, and solving drug-related problems or negative clinical outcomes. Such processes should be carried out in collaboration with the patient and other healthcare professionals, aiming to achieve specific outcomes that improve the patient’s life quality [14]. The Dader Method is a tool to carry out pharmaceutical care, so pharmacists may achieve the greatest possible effectiveness and safety of pharmacotherapy, and, in collaboration with the healthcare team, the patient, and the patient’s family, improve the quality of life in outpatients diagnosed with BD-I [15-17]. The aim of the present study is to assess the effectiveness of the Dader Method for pharmaceutical care in reducing the use of healthcare services (number of hospitalizations, emergency consultations, and unscheduled outpatient consultations) and increasing the effectiveness and safety of treatment in patients with BD-I who are discharged from or referred by the outpatient service of the San Juan de Dios Clinic (SJDC).

## Methods/design

### Study design

A 12-month, randomized, controlled, prospective, single-center clinical trial will be performed to compare the effect of the Dader Method of pharmaceutical care with the usual care process of patients in a psychiatric clinic.

### Study setting

The study is conducted in outpatients with BD-I who attend psychiatric consultation in the Hospital Order San Juan de Dios, which belongs to the SJDC, an institution recognized for its dedication to mental illness care. The clinic has a psychiatric area with 115 beds and a weekly average of 90 consultations of outpatients with mental disorders, such as depression, anxiety disorders, bipolar disorders, panic disorders, hyperactivity, mental retardation, and schizophrenia. The clinic is located in La Ceja, a municipality in the east of Antioquia, an area historically linked to a high prevalence of mental disorders as a result of inbreeding, which determines the selection of individuals with predisposing genetic factors [18-20], and other situations like psychoactive substance use disorders, alcohol, violence, poverty, and stress.

### Study population

The researchers will recruit 200 volunteer patients diagnosed with BD-I, based on the Diagnostic and Statistical Manual of Mental Disorders, 4th edition (DSM-IV). BD-I patients are more likely to have poor adherence, rapid cycling, suicide attempts, and current anxiety or alcohol use disorder. Psychiatrists will refer patients who might meet the inclusion criteria to the pharmaceutical care program; subsequently, the pharmacist will evaluate whether each patient meets all the inclusion criteria and none of the exclusion criteria, and then invite the patient to participate in the study.

The inclusion criteria will be the following:

• Male or female, between 18 and 65 years of age, and diagnosed with BD-I based on the Diagnostic and Statistical Manual of Mental Disorders, 4th edition (DSM-IV), who have been discharged from or referred by the outpatient service of the SJDC.

• Living in Medellín, Sabaneta, Envigado, Itagüí, Bello, Copacabana, Girardota, Barbosa, Guarne, Rionegro, Marinilla, La Ceja, El Carmen de Viboral, El Retiro, San Vicente, La Unión, and El Santuario (Antioquia, Colombia).

The exclusion criteria will be the following:

• Patients with their first manic episode, schizoaffective disorder, BD-II, cyclothymia, and other bipolar spectrum disorders, personality disorders that seem like BD, and sociopathic disorder.

• Patients with epilepsy, infected with the HIV, chronic decompensated disease (blood pressure values above 180/110 mmHg, total cholesterol above 300 mg/dL, low density cholesterol greater than 160 mm/dL, hemoglobin A1c greater than 9%, oxygen saturation lower than 90%).

• Patients unable to comply with the protocol requirements, including severe alcohol and drug use.

• Pregnancy or breastfeeding.

• Patients with intellectual disability, presence of any cognitive impairment impeding the comprehension and signature of the informed consent form, or illiteracy.

• Patients who refuse to sign the informed consent form (consent must be obtained before any study-related procedures are conducted).

• Patients in electroconvulsive therapy.

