### Randomization

Patients will be assigned to the intervention or the control group through a computer-generated randomization - designed by a person external to the study and otherwise unrelated to it - using Microsoft ® Excel 2007. Participants will be assigned to the treatment groups in sequential order, and the randomization list will be strictly confidential (randomization list maintained off-site by the study coordinator, only one person outside the study knows it). The software generates a sequence of 500 random numbers without repetition (1 to 500), assigning a control group code to 250 numbers and an intervention group code to the other 250. Subsequently, the numbers generated are automatically sorted in ascending order to determine each patient’s allocation to one of the two study groups. Participants will be assigned to the intervention or the control group in sequential order once the study’s coordinator (the pharmacist) verifies fulfillment of inclusion criteria.

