### Study outcomes

#### *Evaluation/assessment variables/measuring instruments*

The primary outcomes to be measured are: (1) the number of hospitalizations; (2) the number of emergency service consultations; and (3) the number of unscheduled outpatient visits. In addition to the information provided by patients and family members about the primary objective, the pharmacist gets the information from the records of medical history of the patients, provided by SJDC.

The secondary outcomes to be measured are: (1) adherence to treatment through serum lithium levels, serum valproate levels, carbamazepine-serum levels, and by the questionnaire of Morinsky-Green (MG) [21]; (2) life quality through the Quality of Life Scale: The Short Form (36) Health Survey Questionnaire [22]; (3) Clinical Global Impression for Bipolar Modified scale, CGI-BP-M [23]; (4) Young Mania Rating Scale for the evaluation of mania [24]; (5) Hamilton Rating Scale for Depression [25]; (6) drug safety through creatinine, liver transaminases, alkaline phosphatase, complete blood count, fasting glucose, thyroid stimulating hormone levels (TSH), total T4 or total thyroxin levels (T4), weight and cholesterol; (7) problems related to necessity, effectiveness, and security of the pharmacotherapy (NOMs to be identified and measured); (8) drug-related problems in drug therapy effectiveness, and safety; (9) the impact of side effects of antipsychotic drugs on health-related quality of life with a specific self-rated instrument: the ‘Tolerability and quality of Life’ (TOOL) questionnaire [26]; and (10) the patient’s satisfaction with the pharmaceutical care service measured through the patient satisfaction questionnaire on pharmaceutical care [27]. Control and intervention groups will be compared in terms of the proportion of changes from baseline to follow-up at 12 months. The information collected at 3, 6, and 9 months is part of the follow-up period of patients, and these data help to complement the secondary outcomes of the trial. Secondary outcomes will handled in terms of the proportion of changes from baseline to 12 months following.

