### Sample size calculation

The sample size and power were calculated using EpiInfo™ version 6.04 (Centers for Disease Control and Prevention, Atlanta, GA, USA). Assuming readmissions will be 50% in the control group and 30% in the intervention group, with a confidence of 95% and a power of 80%, it would be required to include at least 166 patients. The estimated sample size of 200 patients with a BD-I diagnosis is needed to cover losses during the follow-up and to increase sensitivity towards secondary objectives.

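### Entry route (discharge or outpatient referral) is neither a randomization stratum nor a named covariate, which costs some precision, and the assumed readmission rate is not tied to the mixed population

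*Protocol article*

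**What the plan says.** - **Eligibility** (Study population). Patients qualify if they are among those "who have been discharged from or referred by the outpatient service of the SJDC". No time limit since discharge is given, and no expected share of each route. Patients in a first manic episode are excluded.
- **Randomization.** One computer-generated list of 500 numbers is used, "assigning a control group code to 250 numbers and an intervention group code to the other 250". "Participants will be assigned to the treatment groups in sequential order"; no stratification factor is mentioned. About 200 patients are to be recruited.
- **Outcome** (Study outcomes). "The primary outcomes to be measured are: (1) the number of hospitalizations", followed by emergency consultations and unscheduled outpatient visits. Arms are to be compared on change from baseline to 12 months.
- **Sample size calculation.** "Assuming readmissions will be 50% in the control group and 30% in the intervention group", with 95% confidence and 80% power, "it would be required to include at least 166 patients"; the number is raised to 200 to cover losses.
- **Biostatistical considerations.** Between-arm tests are chi-square or Fisher, t and Mann-Whitney. Within-arm change is tested by McNemar and paired t-tests. Multivariable models related to the primary outcome are also planned. Their listed variables include severity, polarity of the last episode, comorbidity, education, rural residence, insight and family support. Entry route is not on the list. Hospitalizations and readmission appear there as separate items, and neither is defined.

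**The concern.** A patient leaving hospital and a patient referred from outpatient care can be at different points of an illness whose episodes are, in the article's own description, "usually separated by asymptomatic intervals". If their 12-month admission risks differ, entry route is a prognostic factor that is available when eligibility is checked. An unstratified list lets its share drift apart between arms by chance, and unadjusted tests leave the resulting variation in the error term.

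Two related points follow.

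- The trial is sized on a readmission rate. The article does not say whether 50% is meant for the mixed population, or what readmission means for someone who did not enter from an admission. If the pooled control risk is lower, power is lower.
- If the admission that preceded entry counts in the baseline figure, hospitalizations can fall within an arm without any effect of the intervention.

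**Working it through.** **1. The plan's own figure.** Inputs from the sample size section: 50% versus 30%, 80% power. Per arm, n = [z(α)·√(2·0.4·0.6) + 0.8416·√(0.5·0.5 + 0.3·0.7)]² / 0.20².

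- Two-sided 5%: (1.96·0.6928 + 0.8416·0.6782)² / 0.04 = 93, total 186 (206 with continuity correction).
- One-sided 5%: 74, total 148. With continuity correction: 83, total 166.

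The stated 166 therefore appears only with a one-sided test and continuity correction, whereas the analysis section specifies two-tailed tests. That is a separate matter. At 100 per arm, two-sided power is about 83%, which is the reference below.

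**2. Size of chance imbalance.** Assumptions, not in the article: half of the patients enter by each route; 100 analysed per arm.

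- SD of the between-arm difference in share discharged = √(2·0.5·0.5/100) = 0.0707; 95% range ±1.96·0.0707 = ±13.9 points.
- Shift in the observed risk difference = imbalance × risk gap between routes: 0.139·0.20 = 2.8 points, 0.139·0.30 = 4.2, 0.139·0.40 = 5.5.
- For scale: the standard error with 50% in both arms is √(2·0.25/100) = 7.1 points, and the planned effect is 20 points.
- If 30% rather than 50% enter from discharge, the range is ±12.7 points and the shifts are 2.5 to 5.1 points.

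**3. Effect on the test.** Simulation with 100 per arm, 50/50 mix, control risk 50% ± half the gap and intervention risk 30% ± half the gap. The pooled chi-square test is compared with a Mantel-Haenszel test stratified by route.

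| Assumed gap | Type I, pooled | Type I, stratified | Power, pooled | Power, stratified |
|---|---|---|---|---|
| 10 points | 5.6% | 5.1% | 83.2% | 83.1% |
| 20 points | 5.6% | 5.0% | 83.2% | 84.4% |
| 30 points | 5.6% | 5.0% | 83.2% | 86.4% |
| 40 points | 5.6% | 5.0% | 83.2% | 89.3% |

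Pooled type I error is 5.7% with no gap at all, so the excess over 5% comes from discreteness and not from route.

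Robustness shows when one conditions on a bad draw. In the roughly 9% of trials with an imbalance of at least 10 points in one given direction, pooled type I error is 6.5%, 8.3% and 10.7% at gaps of 20, 30 and 40 points. The stratified test stays at about 5%.

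**4. If 50% applies only to discharged controls.** Assumptions: 50/50 mix, relative risk 0.30/0.50 = 0.6 in both routes, 100 per arm, two-sided 5%. Pooled control risk = 0.5·0.50 + 0.5·(risk in referred controls).

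| Risk in referred controls | Pooled risks | Power | Total N for 80% |
|---|---|---|---|
| 50% | 50% v 30% | 83% | 186 |
| 40% | 45% v 27% | 76% | 222 |
| 30% | 40% v 24% | 68% | 266 |
| 20% | 35% v 21% | 60% | 322 |

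**5. Change from baseline.** No look-back window for baseline hospitalizations is stated. If it includes the admission that led to entry, a fall is partly built in by selection. Randomization makes that fall the same in both arms in expectation, so it cancels between arms. It does not cancel in the McNemar or paired tests.

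**The case against.** The strongest reply is that nothing here is invalid. Simple randomization needs no stratification, the sampling error of an unadjusted test already includes chance imbalance, and step 3 confirms that overall type I error does not move with the risk gap. That stands, and it limits the point to precision and robustness.

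The risk gap and the mix are assumptions. The eligibility wording can even be read with both verbs attached to the outpatient service, and without a time limit a referred outpatient may also have been discharged earlier. That stands too, and is why ranges are given.

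Multivariable models are planned, some listed variables (severity, polarity, insight) may carry part of the prognosis linked to route, and a final covariate set may sit in an analysis plan not shown. This stands in part. The article does name a covariate list, and route is not in it. It describes those models as explaining associated factors, not as the adjusted treatment comparison.

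Three stronger readings are tempting but unsupported:

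- *Chance imbalance biases the primary result.* It does not, as above.
- *Readmission can apply only to discharged patients.* The primary outcome counts hospitalizations in everyone, and because first manic episodes are excluded, referred patients may have earlier admissions. The term is undefined, which is a lesser defect.
- *Change from baseline distorts the between-arm comparison.* Any selection effect falls on both arms alike.

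**Conclusion.** The point holds as a recommended improvement, not as an error that invalidates the analysis. Two entry routes are pooled, the list is unstratified, the stated between-arm tests are unadjusted, and route is absent from the named covariates. With an assumed 50/50 mix and 100 per arm, allowing for route gains about 1 to 6 points of power at assumed risk gaps of 20 to 40 points, and essentially nothing at 10. It also protects the result in the minority of trials with a marked imbalance.

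The loose link between the readmission assumption and the enrolled population could matter more. Power would fall to between 76% and 60% if referred controls had risks of 40% to 20%. That is conditional on the 50% applying to discharged patients only, which the article neither says nor excludes. The caution on change from baseline applies to the within-group tests alone.

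**What to change.** - Record entry route at baseline (discharge from an admission, or outpatient referral), with a written definition. For patients already enrolled, take it from the clinic records that the trial already uses.
- Before unblinding, prespecify route as a covariate, or as a Mantel-Haenszel stratum for a proportion, in the primary between-arm comparison of hospitalizations.
- Report the effect by route as descriptive only; the trial is not sized for subgroup conclusions.
- In the sample size section, state what counts as readmission for a referred patient and whether 50% is meant for the mixed population.
- Rest the conclusion on the between-arm comparison over follow-up. Do not present McNemar or paired tests of within-arm change in hospitalizations as evidence of effect.
- Optional: for patients not yet randomized, have the external person generate randomly varied blocks within route. The first patient was randomized on 24 November 2011, so much of the list may already be used.

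The cost is one extra covariate, a few sentences and slightly more analysis work, with no extra patients or visits. The optional blocks would need two lists instead of one.
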